**6．Receive**

The central laboratory personnel should check the blood samples, input mark code and storage the blood samples on the day the samples received. At the same time, the status of the sample should be recorded immediately.

**7．Central laboratory**

The central laboratory should complete the detection within 10 working days after receiving the sample; and at the same time, feedback the results to the leader unit and the monitor. The monitor should feedback the results to the corresponding research center within one week of receiving the test results.

Contact man: [name], Medical Department of Yiling Pharmaceutical

[contact]

Email: [contact]

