| **Outcome Measures** | Primary endpoints | The composite endpoint events consisting of cardiovascular death and re-hospitalization due to the worsening of heart failure |
| Secondary endpoints | 1. All-cause mortality 2. Secondary endpoint events (given up treatment due to worsening heart failure, successful resuscitation after cardiac arrest, malignant arrhythmia, non-fatal stroke) 3. The incidence of cardiovascular death and re-hospitalization due to worsening heart failure in patients with ischemic heart disease 4. Serum NT-proBNP decrease rate |
| Safety objective and measure | To evaluate the safety and tolerability of QLQX in this patient population;  Changes in clinical chemistry/haematology parameters, ECG, physical examination, any forms of adverse events (AEs) |
| **Statistical methods** | The primary objective of the study is to determine the superiority of QLQX versus placebo in reducing the incidence of the primary composite endpoint. The random distribution ratio is 1:1 between study group and control group. The sample size is in estimating the incidence of composite endpoint events for 25% during the follow-up period of 36 months. In total 3080 cases were expected to enroll (1540 patients per group) with 620 composite endpoint events should be observed. | |
| **Statistical unit** | Peking University Clinical Research Institute | |
| **Dosage and mode of administration** | Study group: Standardized treatment of chronic heart failure + Qiliqiangxin Capsules, 4 capsules/time, 3 times/day, take orally  Control group: Standardized treatment of chronic heart failure + Placebo Capsules, 4 capsules/time, 3 times/day, take orally | |
| **Duration of treatment** | The patient was enrolled with observation event as the index. The planned enrollment time was 2 years and the drug was taken for at least a year. | |
| **Expected progress** | August 2018 to August 2021 | |

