Traditional Chinese medicine (TCM) has accumulated rich experience in the long-term medical practice of preventing and treating heart failure, and its understanding of heart failure is also deepening. There have been some researches and reports on the treatment of heart failure with TCM. The researches on the treatment of heart failure by Chinese medicine QiliQiangxin Capsules was initially successful. The research results were published in an international journal of cardiovascular disease JACC in 2013[15] and received the attention and praise from worldwide scholars. All enrollees were treated with standard-optimized treatment, and the ratio of serum amino-terminal B-type natriuretic peptide precursor (NT-proBNP) was significantly lower in the Qiliqiangxin capsule group compared with the placebo group, higher ratio of patients with a decrease of >30% and lower incidence of adverse events were observed, indicating that Qiliqiangxin Capsules is effective and safe in the treatment of chronic heart failure. Qiliqiangxin Capsules became the first proprietary Chinese medicine to be included in the Guidelines for the Diagnosis and Treatment of Heart Failure in China 2014 and 2018.

Qiliqiangxin Capsules is the first to explore the pathogenesis and treatment of chronic heart failure with the theory of collateral disease, which proposes insufficiency of the heart-qi as the basis of TCM. Meanwhile, obstruction of collaterals is the central link. The fluid does not flow and exudes from veins which the blood stasis and water stasis blocks the veins, inducing edema [16]. The theory is similar with a new concept proposed by modern medicine in recent years that the hemodynamic changes caused by early neuroendocrine activation can lead to ventricular remodeling, which is the basic mechanism for the development of heart failure.

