Due to the post-marketing unique advantages of Qiliqiangxin Capsules in the clinical application, it has become a hot spot for many experts and scholars in China. Previous studies have shown that the drug has cardiotonic and diuretic effect, can improve the heart function of CHF rats, and increase water discharge by reducing the expression of AQP2 in the kidney [17]. It also can reduce the expression of AngII and periostin proteins in rats with heart failure after myocardial infarction and is dose-dependent [18]. The mechanism of the effect of Qiliqiangxin Capsules on improving cardiac function is related to its inhibition of myocardial remodeling [19]. Reducing the pro-inflammatory factors of cardiomyocytes and increasing the immunomodulatory effects of anti-inflammatory factors may be one of the immunopharmacological mechanisms of Chinese medicine for improving heart function in AMI rats [20]. In the clinical study of taking Qiliqiangxin Capsules for the treatment of patients with chronic congestive heart failure, it is indicated that Qiliqiangxin Capsules can improve cardiac function grading, heart failure (Lee’s) score, systolic and diastolic function, ejection fraction (EF), TCM syndrome differentiation (中医证候), quality of life and other curative indicators and safety indicators, elevate blood nitric oxide (NO) and calcitonin gene-related peptide (CGRP) levels, and decrease endothelin (ET) levels; thereby significantly improving endothelial function in patients with heart failure.

In summary, Qiliqiangxin Capsules could resolve the current problems and eliminates the essential causes that treat cardiac insufficiency from multiple pathways, multiple links and multiple targets. It reflects the advantages of compound Chinese medicine in treating heart failure from the overall treatment, and significantly reduces NT- ProBNP levels, indicating improvement of the patient's long-term prognosis. This study is a large randomized, double-blind, multi-center clinical study carried out on the basis of achieving major study results with NT-proBNP as a surrogate endpoint, adopts the incidence of composite endpoint events consisting of cardiovascular death and re-hospitalization for heart failure as the study endpoints, in order to collect the evidence-based medical evidences for long-term prognosis in patients with chronic heart failure.

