# 3.2.2 Randomization and Treatment period (day 0 to 12 months [with maximum of 36 months]):

The dispensing date of the IPs is regarded as day 0. Patients will be randomized into the study or control group in a 1:1 ratio w

ith the basis of current standardized treatments for chronic heart failure. The study drug is recommended to be taken about 30 minutes after meals, three times a day as follow.

-Study group: Standardized treatment of chronic heart failure + Qiliqiangxin Capsules (4 capsules/time, 3 times/day);

-Control group: Standardized treatment of chronic heart failure + Placebo Capsules (4 capsules/time, 3 times/day);

This study does not allow dose adjustments. If the patient miss to take the IP in a day, the accumulated dose for the next day should not exceed the daily dose. If the patient has an intolerable adverse event, which is relevant to study drug according to the judgment of researcher, the patient should terminate the following treatment with the study drug.

Do not take drugs at home on the morning of visit day. Investigators will review laboratory results received from the past visit(s). If the patient has experienced any potential endpoints, SAEs, DAEs and/or AEs of interest since the last visit, these should be recorded in the CRF.

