# 6.2 Potential endpoint events

For each potential endpoint event, the investigator or delegate will record information in the CRF

- **Hospitalization for heart failure:**

1. The patient was hospitalized for HF diagnosed preliminarily;

2. The patients who were in hospital extended at least 24 hours (or if the hospitalization time and discharge time were not available, it should indicate change of calendar date);

3. Record on the patient report that there are new symptoms or worsening symptoms due to HF, including at least one of the following:

a. Difficulty breathing (difficulty breathing on exertion, difficulty breathing on resting, orthopnea, paroxysmal breath with difficulty at night)

b. Reduced exercise tolerance

c. Fatigue

4. The patient had objective evidence of an acute exacerbation of HF, including at least two health examination results or a health examination result and at least one laboratory standard, including:

a. Determine the health examination results caused by HF, including new or deteriorated:

1) Peripheral edema; 2) Abdominal distension or increase of ascetic fluid (in the absence of primary liver disease); 3) Lung rales and/or crackles; 4) Increased jugular venous pressure and/or hepatojugular reflex (+); 5) S3 galloping; 6) Clinically significant or rapid weight gain, having relation with fluid retention;

b. Laboratory evidence of new or worsening HF obtained within 24 hours, including:

1) Increased concentration of B-type natriuretic peptide (BNP) / N-terminal B-type natriuretic peptide precursor (NT-proBNP) consistent with acute decompensated HF (eg.: BNP > 500 pg/ml or NT-proBNP > 2000 pg/ml); In patients with long-term elevation of natriuretic peptides, special attention should be paid to a significant increase beyond baseline. 2) Imaging evidence of pulmonary congestion; 3) Non-invasive diagnostic evidence of clinically significant increase in left or right ventricular filling pressure or decreased cardiac output; echocardiographic criteria includes: E/e ́>15 or D leading pulmonary venous inflow pattern, congestive inferior vena cava with minimal inspiratory collapse, or reduction of small stroke distance (time velocity integral; TVI) at left ventricular outflow (LVOT). 4) Invasive diagnostic evidence: right heart catheterization showed pulmonary capillary wedge pressure (pulmonary occlusion pressure) ≧ 18mmHg, central venous pressure ≧ 12mmHg, or cardiac output index;

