**NT-proBNP** **sample preparation process**

Draw 3ml venous blood from each subject

EDTA anticoagulation

Centrifuge to obtain the supernatants

Label the blood samples of each patient

Storage in the refrigerator at -20℃

All samples should be sent for test within 3 months after collection

Note:

1. It should be detected in the condition of no inflammation nor infection (metabolic stability) to reduce individual differences;
2. Patient preparation: Fasting for more than 12 hours, collecting venous blood in the sitting position at 8:00 am to 9:00 am.
3. Blood collection requirements: Use a vacuum blood tube with separation gel (usually yellow cap) to collect 6 ml of venous blood; avoid the occurrence of hemolysis and lipemia (If any, please specify).
4. Serum separation: 30 minutes after the collection of specimen, the specimen should centrifuge at the speed of 3000 rpm for 5 minutes within 2 hours. Divide supernatant into two collection tube without any additives, each tube should not less than 800μl. One tube sent to the central laboratory for detection, and storage the other tube as reserved sample. Attach the same number as registration form (Table 1), including name, gender, age, specimen collection time and collection unit.
5. Transportation and preservation of serum samples: serum frozen specimens should be placed in a low temperature refrigerator at -20 °C, the maximum of retention period is 6 months. Serum samples should be placed in a dry ice box while transportation. The refrigerator temperature should be recorded daily for future reference.

Table 1 Reserved sample record table and label manuscript

| Random No. | Patient name | Sex | Age | Blood collection date |
| --- | --- | --- | --- | --- |
|  |  |  |  |  |
| Hospital (detection of NT-proBNP in Qiliqiangxin study) | | | |  |

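### Appendix 2 returns central NT-proBNP results to the lead unit, monitor and sites without limiting this to baseline, and no rule masks on-treatment values of a marker the drug is expected to lower

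*Protocol*

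**What the plan says.** Appendix 2, section 7, gives the central laboratory 10 working days from receipt to finish the assay and to "feedback the results to the leader unit and the monitor". The next step is: "The monitor should feedback the results to the corresponding research center within one week of receiving the test results". Neither sentence restricts the flow to screening or baseline samples.

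On timing, the sample-preparation part of Appendix 2 says: "All samples should be sent for test within 3 months after collection". Its record table identifies each sample by random number and patient name.

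Section 3.2.2 tells investigators, at treatment-period visits, to go over laboratory results that have come in from earlier visits. It names no exception.

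Post-randomisation values must exist, because the synopsis lists "Serum NT-proBNP decrease rate" as a secondary endpoint.

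On the expected effect, section 1.3 reports that in the earlier placebo-controlled study NT-proBNP "was significantly lower in the Qiliqiangxin capsule group compared with the placebo group", with a larger share of patients falling by more than 30%. It concludes that the drug "significantly reduces NT- ProBNP levels, indicating improvement of the patient's long-term prognosis".

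Section 8 covers matching capsules, coded labels, emergency unblinding, and the blinding of analysis staff until database lock. It contains nothing on biomarker results.

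**The concern.** Matching capsules do not protect a double-blind trial fully if a marker that the drug is thought to move is reported back to the people making outcome-relevant decisions. The primary endpoint includes re-hospitalisation for worsening heart failure, and whether to admit is partly a matter of judgement. The site also decides what to submit as a potential endpoint, and it may change background therapy if the reason is recorded (section 3.3.1). A known NT-proBNP value can bear on any of these, either by suggesting the arm or simply because a low or high number reassures or alarms.

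Adjudication by two committee members (section 6.1) gives only partial protection. It cannot recover an admission that never took place. Appendix 3 also includes laboratory results in the material sent for adjudication, with nothing that keeps on-treatment central NT-proBNP out of it.

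**Working it through.** The point is textual, and the protocol gives no figure to reproduce.

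**1. Can on-treatment results reach sites while patients are still at risk?** The longest path in Appendix 2 is 3 months to dispatch, 24 hours with the courier, 10 working days in the laboratory and one week through the monitor. That is about 3 months and 3 weeks. Minimum follow-up is 12 months (sections 2.1 and 2.2). A sample taken in roughly the first 8 months after randomisation would therefore be back before even the last-enrolled patient finishes. The visit table in section 5 is a figure that is not available here, so the number and timing of later samples cannot be read. The secondary endpoint implies at least one.

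**2. Is there a rule elsewhere that stops this?** Sections 8.1, 8.1.1, 8.2 and 8.2.1, section 6.1 and Appendix 3 contain none.

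**3. How informative is one result?** The protocol gives neither the between-arm difference in NT-proBNP change nor its spread, so both are assumed: a between-arm ratio r of 0.7 to 0.9, and a standard deviation of the individual log change of 0.5 to 0.9. With a cut midway between the arms, the chance of naming the right arm is Φ(|ln r| / (2·SD)).

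- r = 0.7, SD = 0.5: Φ(0.357/1.0) = 0.64
- r = 0.8, SD = 0.7: Φ(0.223/1.4) = 0.56
- r = 0.9, SD = 0.9: Φ(0.105/1.8) = 0.52

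Chance is 0.50, so a single value is a weak-to-moderate clue.

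**4. How strongly would sites have to react for this to matter?** Suppose a low value appears in a share p of the drug arm and 1 − p of the placebo arm, and that sites admit or report a fraction x less often when they see one. The ratio of counted events is (1 − p·x)/(1 − (1 − p)·x).

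- p = 0.64: a 5% deficit needs x = 0.05/(0.64 − 0.95·0.36) = 0.05/0.298 = 17%. A 10% deficit needs x = 0.10/(0.64 − 0.90·0.36) = 0.10/0.316 = 32%.
- p = 0.52: a 5% deficit needs x = 0.05/(0.52 − 0.95·0.48) = 0.05/0.064 = 78%. A 10% deficit would need x above 100%, so it cannot occur.

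Nothing in the protocol shows how sites would react.

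**5. Does the central value itself qualify an endpoint?** Section 6.2 lists raised natriuretic peptide among the laboratory evidence for a heart-failure hospitalisation and adds: "In patients with long-term elevation of natriuretic peptides, special attention should be paid to a significant increase beyond baseline". But that evidence must be obtained within 24 hours, and a central result takes weeks to months. The item is also optional, since two examination findings satisfy the criterion without it. The plausible route is knowledge of the patient's course, not the central value serving as the qualifying test.

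**The case against.** A reader might draw four stronger conclusions, and the documents support none of them.

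- **A quantified inflation of type I error.** With a true hazard ratio of 1, 620 events and a one-sided level of 0.02314, losing 5% of drug-arm events would raise the error to Φ(√(620/4)·|ln 0.95| − 1.993) = 8.8%. The arithmetic is right, but the 5% is invented. Step 4 of the working shows that it needs a reaction of 17% even at the most informative end of the assumed range. The formula also treats a suppressed event as lost for good, whereas in a time-to-first-event analysis the patient may still be counted later.
- **A bias that favours the drug.** High or rising values, expected more often on placebo, could equally prompt recorded changes in background therapy. That would lower placebo events and pull the comparison towards no difference. The net direction is open.
- **Routine study results feeding the primary endpoint directly.** The 24-hour window and the slow turnaround make this unlikely. The comparator in section 6.2 is the patient's baseline value, which sites may properly hold.
- **A run of serial values for each patient.** The visit table is unavailable and only one later value is implied.

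The protocol also limits non-reporting. Section 6.1 asks for all deaths and all heart-failure events, urgent visits included, to be submitted for adjudication, with supporting documents collected within 7 days. Section 11 requires case report forms to agree with source records. An admission that occurred is hard to lose, so the exposure lies mainly in the decision to admit and in background treatment.

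These points lower the weight of the concern. They do not supply a masking rule or a reason to release on-treatment values to sites, the lead unit and the monitor.

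**Conclusion.** The concern holds as an avoidable weakness in blinding. As written, the plan sends on-treatment values of a marker that it expects the drug to lower to the people whose judgement helps to generate primary events, and no text withholds them. Under the assumed ratios and spreads, one value is a weak-to-moderate clue (52% to 64% correct). The size and net direction of any effect on the hazard ratio or on the error rate cannot be derived from the protocol, and no figure should be attached to either. Returning the screening or baseline result is legitimate, because the entry criterion of at least 450 pg/ml calls for it. The defect is only that release is not restricted after randomisation. This is a cheap improvement worth making, not a flaw that invalidates the design.

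**What to change.** Amend Appendix 2, section 7, so that only the screening or baseline NT-proBNP result goes back to sites. Hold all post-randomisation central results from sites, monitors, the lead unit, the sponsor and the adjudicators until database lock. Release them before then only to the independent interim-analysis and safety committee (called DSMC in section 2.7 and DSMB in section 9.3). Except NT-proBNP from the review of laboratory results in section 3.2.2, and add a sentence to section 8.1 naming the masking of this marker as part of the blinding. Natriuretic peptide tests ordered locally for clinical reasons stay available for care and for adjudication.

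The cost is a wording change and a change to the laboratory's reporting route. Sites lose routine study NT-proBNP values. Local testing leaves some residual leakage, so the change closes most of the gap but not all of it.

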**8. Conversion between different units**

1 pg/ml = 0.118 pmol/L

pg (picogram), pmol (picomolar)

# Appendix 3: Endpoint event report process

**Researcher** Report relevant evidences and materials (medical records, laboratory results, etc) within 7 days in CRF

**CEC Secretary**  (Email) *****@***.com

Complete evidence

**Member**  (Email) Two members were appointed in turn for judgment, and the conclusion was recorded in the report.

Lack of Reserve the signed report,

evidence sent to the study secretary by email

**CEC secretary**

Inconsistency Consistency, and reply to the reporter

Save and registration

Review Researcher Record events or report SAE based on the conclusion
